#### Secondary outcome measures

Secondary outcomes include: functional and clinical outcome, expressed by mRS and MGS scores, respectively, at discharge, at 2 weeks, at 3, 6 and 12 months after start of study treatment. We will also determine a utility-weighted mRS (UW-mRS) at 3 months. The GOSE score will be assessed at 3 months, quality of life (expressed by SF-36 and QOLIBRI) at 3 and 12 months, cost-effectiveness at 3 and 12 months and haematoma thickness at 2 weeks. During the first 12 months, we will evaluate haematoma recurrence (defined as recurrence of symptoms and neurological signs after initial improvement with persistence, recurrence or increase of CSDH on follow-up CT), failure of therapy after randomisation and requiring intervention, complications and drug-related adverse events, duration of hospital stay and healthcare and productivity costs in both patient groups. Finally, we will evaluate mortality during the first 3 and 12 months.

### Randomisation

Patients are randomised in a 1:1 allocation ratio stratified for study site by their treating physician. Stratified block-randomisation is done by using a computer randomisation algorithm to generate balanced random samples (Castor EDC, Ciwit B.V., Amsterdam, The Netherlands).

### Sample size

This RCT is designed as a non-inferiority study. The sample size for showing non-inferiority is calculated based on a simulation programme in R statistical software for power for ordinal regression. We aim to include 420 patients. This sample size yields a power of 90%, assuming that the true effect of DXM is an odds ratio 1.15 for a better functional outcome on the mRS, and the limit for inferiority is an odds ratio < 0.9.

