## Abstract

**Background:**

Chronic subdural haematoma (CSDH) is a common neurological disease with a rapidly rising incidence due to increasing age and widespread use of anticoagulants. Surgical intervention by burr-hole craniotomy (BHC) is the current standard practice for symptomatic patients, but associated with complications, a recurrence rate of up to 30% and increased mortality. Dexamethasone (DXM) therapy is, therefore, used as a non-surgical alternative but considered to achieve a lower success rate. Furthermore, the benefit of DXM therapy appears much more deliberate than the immediate relief from BHC. Lack of evidence and clinical equipoise among caregivers prompts the need for a head-to-head randomised controlled trial. The objective of this study is to compare the effect of primary DXM therapy versus primary BHC on functional outcome and cost-effectiveness in symptomatic patients with CSDH.

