**Methods/Design:**

This study is a prospective, multicentre, randomised controlled trial (RCT). Consecutive patients with a CSDH with a Markwalder Grading Scale (MGS) grade 1 to 3 will be randomised to treatment with DXM or BHC. The DXM treatment scheme will be 16 mg DXM per day (8 mg twice daily, days 1 to 4) which is then halved every 3 days until a dosage of 0.5 mg a day on day 19 and stopped on day 20. If the treatment response is insufficient (i.e. persistent or progressive symptomatology due to insufficient haematoma resolution), additional surgery can be performed. The primary outcomes are the functional outcome by means of the modified Rankin Scale (mRS) score at 3 months and cost-effectiveness at 12 months. Secondary outcomes are quality of life at 3 and 12 months using the Short Form Health Survey (SF-36) and Quality of Life after Brain Injury Overall Scale (QOLIBRI), haematoma thickness after 2 weeks on follow–up computed tomography (CT), haematoma recurrence during the first 12 months, complications and drug-related adverse events, failure of therapy within 12 months after randomisation and requiring intervention, mortality during the first 3 and 12 months, duration of hospital stay and overall healthcare and productivity costs. To test non-inferiority of DXM therapy compared to BHC, 210 patients in each treatment arm are required (assumed adjusted common odds ratio DXM compared to BHC 1.15, limit for inferiority < 0.9). The aim is to include a total of 420 patients in 3 years with an enrolment rate of 60%.

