### Data analysis

The primary effect parameter (and all other comparisons of the treatment arms) will be performed on all randomised subjects according to the intention-to-treat (ITT) principle. A sensitivity analysis is performed for the primary outcome measure in a per-protocol fashion, defined as patients in the ITT population receiving treatment as randomised without protocol violation.

The primary effect parameter will be the adjusted common odds ratio (acOR) for a shift in the direction of a better outcome on the mRS at 3 months with 95% confidence interval, estimated with multivariable ordinal logistic regression with adjustment for important prognostic baseline variables. This analysis is becoming the standard for ordinal functional outcomes in neurology and neurosurgery, supported by evidence for its maximisation of statistical power while maintaining interpretability. Missing data in baseline characteristics will be imputed using multiple imputation (*n* = 10) based on the outcome and relevant baseline covariates using the ‘Multivariate Imputation by Chained Equations’ (MICE) algorithm. Patients with missing primary outcome will be excluded but every effort will be made to obtain follow-up. To accept the null hypothesis (H0) of non-inferiority the lower 95% confidence limit of the odds ratio for a better functional outcome on the mRS of DXM versus surgery should be equal to or above 0.9.

Furthermore, we will perform an extensive economic evaluation of DXM versus surgery for patients with a CSDH. The economic evaluation will be performed according to the Dutch guidelines, using a societal perspective. The timeframe will be 12 months to take all relevant costs and effects into account. The primary effect measure for the economic evaluation will be functional status (mRS). Secondary outcome measures for the cost-effectiveness analyses (CEA) will be mortality and quality-adjusted life year (QALY), based on the 12-month SF-36 and QOLIBRI summary scores. The cost-effectiveness will be assessed by calculating the incremental cost-effectiveness ratio (ICER), defined as the difference in costs, divided by the average change in effectiveness of DXM versus surgery in CSDH patients. The cost-effectiveness analysis will use the mRS as effect measure and the cost-utility analysis will use the QALY as effect measure.

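### The stated 90% power cannot hold: with 420 patients, a true odds ratio of 1.15 and the rule that the lower 95% limit must reach 0.9, power is at most 30.5%

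*Protocol article*

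**What the plan says.** The Sample size section bases its figure on a simulation programme for ordinal regression. It gives the target ("We aim to include 420 patients") and the claim: "This sample size yields a power of 90%, assuming that the true effect of DXM is an odds ratio 1.15" for better function on the mRS, with inferiority set at an odds ratio below 0.9.

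The Methods/Design part of the Abstract repeats the inputs, calls 1.15 the adjusted common odds ratio, and concludes that "210 patients in each treatment arm are required". It gives no power figure. The Randomisation section confirms the allocation: "Patients are randomised in a 1:1 allocation ratio stratified for study site".

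The Data analysis section sets the primary analysis as multivariable ordinal logistic regression of the 3-month mRS, reported as an acOR with a 95% confidence interval. Its decision rule begins "To accept the null hypothesis (H0) of non-inferiority the lower 95% confidence limit of the odds ratio" and requires that limit to be 0.9 or higher.

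**The concern.** An odds ratio of 1.15 is close to a margin of 0.9, and 420 patients is a modest number for an ordinal outcome. For 90% power against a lower 95% limit, the assumed effect must lie 1.96 + 1.28 = 3.24 standard errors above the margin. Here it lies less than 1.5 standard errors above.

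The primary efficacy conclusion is at stake. A reader who trusts the 90% would take a failed test as strong evidence that DXM is not good enough. If power is really about 30%, failure is the expected result even when DXM is somewhat better than surgery.

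**Working it through.** **Inputs from the protocol article**
- N = 420, 210 per arm, 1:1 (Sample size; Abstract; Randomisation).
- True acOR 1.15, margin 0.9 (Abstract; Sample size).
- Success: lower 95% limit of the acOR ≥ 0.9 (Data analysis). I take the interval as two-sided, so z = 1.96, and show the one-sided reading as well.
- mRS distribution and simulation alpha: not given. I therefore use a bound that needs no distribution, then a range of assumed ones.

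**Formula.** Under proportional odds with 1:1 allocation, the information on the log odds ratio is N/12 × (1 − Σp³), where p are the category proportions averaged over the arms. Since Σp³ > 0, it is below N/12 = 420/12 = 35. So SE ≥ √(12/420) = 0.169.

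**Attempt to reproduce the 90%**
- Distance to the margin: ln(1.15/0.9) = 0.245.
- In standard errors: at most 0.245/0.169 = 1.45.
- Power, two-sided 95% interval: at most Φ(1.45 − 1.96) = Φ(−0.51) = 30.5%.
- Power, one-sided 95% limit: at most Φ(1.45 − 1.645) = 42%.

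The 90% is not reproduced.

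**Assumed mRS distributions** (surgery arm, scores 0 to 6, in %)

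| Assumed distribution | SE | Power, two-sided 95% | N for 90% power |
|---|---|---|---|
| Uniform | 0.171 | 30.0% | 2,143 |
| 20/25/20/13/8/4/10 | 0.172 | 29.6% | 2,180 |
| 30/34/20/6/3/2/5 (84% in scores 0–2) | 0.176 | 28.5% | 2,277 |
| 50/25/10/5/3/2/5 (concentrated) | 0.184 | 26.6% | 2,482 |
| Bound for any distribution | 0.169 | 30.5% | 2,099 |

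Simulating 1,000 proportional-odds trials for the second and third rows gave 31.1% and 29.2%. The Monte Carlo error is √(0.3 × 0.7/1000), about 1.4 points, so both agree with the formula.

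**Other readings that might rescue the figure**
- One-sided alpha 0.10: at most 57%. One-sided alpha 0.20: at most 73%.
- 420 per arm (N = 840), against the Abstract: at most 54%, or 66% with a one-sided 95% limit.
- mRS dichotomised at 84% favourable: 14%.

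**What the design implies, using the smallest possible SE**
- Observed acOR needed for success: 0.9 × exp(1.96 × 0.169) = 1.25.
- Power if the true odds ratio is 1.0: ln(1/0.9) = 0.105, so at most Φ(0.105/0.169 − 1.96) = 9%.
- N for 90% power: at least 12 × 3.24²/0.245², about 2,100.
- True odds ratio giving 90% power with 420 patients: at least 0.9 × exp(3.24 × 0.169) = 1.56.
- Margin giving 90% power with 420 patients at a true 1.15: at most 1.15 × exp(−3.24 × 0.169) = 0.66.

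**The case against.** The strongest reply is that the article shows neither the simulation's alpha nor its mRS distribution, so 90% need not be the misreported figure; the assumed odds ratio or the margin could be. That much stands: the documents show that 420, 1.15, 0.9, 90% and the lower-limit rule cannot all be true, and do not show how the error arose. It does not save the statement as printed. The bound holds for every mRS distribution, so no unseen detail restores 90% while the other inputs stand. Covariate adjustment does not help either: the Abstract defines 1.15 as the adjusted odds ratio, and the N/12 bound applies to that parameter.

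Several stronger readings are tempting, and the documents do not support them:
- *The simulation counted point estimates instead of lower limits.* The chance that the estimate alone is at or above 0.9 is about 92%, close to 90%. Calling non-inferiority the null hypothesis might seem to fit this. But the simulation is not shown, and the same sentence gives a correct lower-limit rule, so this is conjecture.
- *An odds ratio above 1 contradicts the background.* The Abstract does describe DXM as "used as a non-surgical alternative but considered to achieve a lower success rate". However, the Discussion cites a prospective study with favourable outcome in 88% after DXM alone and 77% after surgery alone (another cited study is less favourable to DXM), and the DXM arm allows additional surgery.
- *The sample size ignores missing outcomes.* Such an allowance is commonly left to the full protocol.
- *The whole trial will be inconclusive.* Cost-effectiveness at 12 months is also a primary endpoint. The result here concerns only the mRS non-inferiority test.

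**Conclusion.** The power statement is wrong as written. Under the plan's own effect, margin and decision rule, 420 patients give at most 30.5% power, about a third of the stated 90%, or at most 42% if a one-sided 95% limit was meant. These two ceilings rest only on proportional odds, 1:1 allocation and a normal approximation. The figure of about 28–30% depends on assumed mRS distributions; a very concentrated one gives 27%.

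If the true acOR is 1.15, the mRS test fails about 70% of the time (1 − 0.305 = 69.5% at best). The Abstract's claim that 210 per arm are required falls with the power figure. The hypothesis labels in the Data analysis section are reversed and should be corrected at the same time, although the rule itself is sound.

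**What to change.** - Re-run the ordinal simulation with success defined as the lower 95% limit of the acOR being at or above 0.9. State the alpha (one- or two-sided) and the assumed mRS distribution.
- In the Sample size section, replace 90% with the power obtained. If the re-run shows that the odds ratio, the margin or the confidence level was misreported, correct that figure instead, so that all five agree.
- In the Abstract, change the claim that 210 per arm are required to match.
- In the Data analysis section, state H0: acOR < 0.9 against H1: acOR ≥ 0.9.
- Add how a failed test will be read: inconclusive if the confidence interval spans 0.9, evidence of inferiority if its upper limit is below 0.9. A blanket rule that every failure is inconclusive would be wrong.

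The cost is one simulation run and a wording amendment, plus a less favourable published power. Correcting the statement needs no change in enrolment, but it does not make the test better powered. Whether the design should stand at its true power is a separate decision for the sponsor.

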### Data collection

All patient data is collected in the electronic data capture software Castor EDC (Ciwit B.V., Amsterdam, The Netherlands). This software allows built-in logical checks and validations to promote data quality. Data entry is performed locally by trained research nurses and physicians. No patient-identifying information is collected.

### Data analysis

The primary effect parameter (and all other comparisons of the treatment arms) will be performed on all randomised subjects according to the intention-to-treat (ITT) principle. A sensitivity analysis is performed for the primary outcome measure in a per-protocol fashion, defined as patients in the ITT population receiving treatment as randomised without protocol violation.

The primary effect parameter will be the adjusted common odds ratio (acOR) for a shift in the direction of a better outcome on the mRS at 3 months with 95% confidence interval, estimated with multivariable ordinal logistic regression with adjustment for important prognostic baseline variables. This analysis is becoming the standard for ordinal functional outcomes in neurology and neurosurgery, supported by evidence for its maximisation of statistical power while maintaining interpretability. Missing data in baseline characteristics will be imputed using multiple imputation (*n* = 10) based on the outcome and relevant baseline covariates using the ‘Multivariate Imputation by Chained Equations’ (MICE) algorithm. Patients with missing primary outcome will be excluded but every effort will be made to obtain follow-up. To accept the null hypothesis (H0) of non-inferiority the lower 95% confidence limit of the odds ratio for a better functional outcome on the mRS of DXM versus surgery should be equal to or above 0.9.

Furthermore, we will perform an extensive economic evaluation of DXM versus surgery for patients with a CSDH. The economic evaluation will be performed according to the Dutch guidelines, using a societal perspective. The timeframe will be 12 months to take all relevant costs and effects into account. The primary effect measure for the economic evaluation will be functional status (mRS). Secondary outcome measures for the cost-effectiveness analyses (CEA) will be mortality and quality-adjusted life year (QALY), based on the 12-month SF-36 and QOLIBRI summary scores. The cost-effectiveness will be assessed by calculating the incremental cost-effectiveness ratio (ICER), defined as the difference in costs, divided by the average change in effectiveness of DXM versus surgery in CSDH patients. The cost-effectiveness analysis will use the mRS as effect measure and the cost-utility analysis will use the QALY as effect measure.

Uncertainty around this ratio will be presented using confidence eclipses on the cost-effectiveness plane and acceptability curves. We will perform a sensitivity analysis to assess the robustness of the results to changes in costs and effectiveness parameters. Due to the short time horizon, no discounting for costs and effects will be used (see Additional file 2 for statistical analysis plan).

For secondary endpoint parameters, Kaplan-Meier and Cox regression analysis will be used for mortality comparisons between the treatment arms, binary logistic regression for complications and failure of therapy, and a linear regression to evaluate quality of life. A *p* value of less than 0.05 will be used to indicate statistical significance. For all analyses, R statistical software will be used.

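### The primary analysis is said to cover all randomised patients, yet patients without a 3-month mRS are dropped and their other planned mRS scores go unused

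*Protocol article*

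**What the plan says.** All references are to the protocol article.

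- **Analysis set (Data analysis).** The primary and all other comparisons are "performed on all randomised subjects according to the intention-to-treat (ITT) principle".
- **Missing outcome (Data analysis, next paragraph).** "Patients with missing primary outcome will be excluded but every effort will be made to obtain follow-up".
- **Missing baseline data (same paragraph).** "Missing data in baseline characteristics will be imputed using multiple imputation", with 10 imputations by MICE and the outcome among the predictors.
- **Sensitivity analysis (Data analysis).** "A sensitivity analysis is performed for the primary outcome measure in a per-protocol fashion". The article names no other for the primary mRS comparison.
- **Other mRS scores (Secondary outcome measures).** Functional and clinical outcome are "expressed by mRS and MGS scores, respectively, at discharge, at 2 weeks, at 3, 6 and 12 months after start of study treatment".
- **Effect measure and margin.** The estimate is the "adjusted common odds ratio (acOR) for a shift in the direction of a better outcome on the mRS at 3 months", so values above 1 favour DXM. Under Sample size, "the limit for inferiority is an odds ratio < 0.9".

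The article states no expected rate of missing 3-month mRS, overall or by arm.

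**The concern.** Once a single 3-month mRS is missing, the set analysed is no longer everyone randomised. The rule also discards scores on the same scale, from the same patient, planned before and after the missing assessment. The imputation method is already specified but stops short of the variable that matters most.

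The trial is open-label in a generally elderly population with comorbidity, and the primary mRS is taken by phone. Failure to respond may therefore be linked to poor status and may differ by arm. Blinding the assessor does not prevent this. The per-protocol analysis cannot show such a bias, because it is a subset of the same population.

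The limit of 0.9 lies only 0.105 from no difference on the log scale, so a small shift counts. The harmful direction is loss of poor-outcome DXM patients, which makes DXM look better than it is.

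**Working it through.** **Inputs from the article.** Limit OR 0.9; 420 patients, 1:1; non-inferiority read from the lower 95% limit, that is one-sided 2.5%. The article gives no figure for missingness to reproduce. The margin is |ln 0.9| = 0.105.

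**Assumed inputs.** True full-arm OR 0.90; fraction missing m in each arm; missing patients have k times the odds of a better outcome compared with observed patients of their own arm; SE of the log OR 0.174. The SE comes from the proportional-odds variance √(12 / (N(1 − Σp̄³))), where p̄ are the mean mRS category probabilities. With N = 420, an SE of 0.174 corresponds to 1 − Σp̄³ = 12 / (420 × 0.174²) = 0.944.

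**Model.** Each full arm is the mixture (1 − m) × observed + m × missing. The observed OR is solved so that a proportional-odds fit to the two full arms gives 0.90. To first order the shift in log OR is (m_DXM − m_BHC) × ln(1/k), which serves as a hand check.

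| Missing BHC / DXM | k | Shift by hand | OR by hand | OR fitted | Share of margin | One-sided error |
|---|---|---|---|---|---|---|
| 5% / 5% or 10% / 10% | 1/2 | 0 | 0.900 | 0.900 or 0.899 | 0% | 2.5% |
| 3% / 5% | 1/2 | 0.02 × 0.693 = 0.0139 | 0.913 | 0.912 | 13% | 3.0% |
| 5% / 10% | 1/2 | 0.05 × 0.693 = 0.0347 | 0.932 | 0.931 | 32% | 3.9% |
| 0% / 10% | 1/2 | 0.10 × 0.693 = 0.0693 | 0.965 | 0.964 | 65% | 5.9% |
| 0% / 10% | 1/3 | 0.10 × 1.099 = 0.110 | 1.005 | 1.00 | about 100% | about 8.8% |

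**Worked row (0% / 10%, k = 1/2).** ln(0.964/0.90) = 0.0687. Share of margin: 0.0687/0.105 = 65%. One-sided error: Φ(−1.960 + 0.0687/0.174) = Φ(−1.565) = 5.9%.

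**Opposite direction.** With 10% missing in BHC and 5% in DXM, the hand formula gives 0.90 × exp(−0.0347) = 0.869. The bias then works against DXM, and the error falls to Φ(−1.960 − 0.0347/0.174) = Φ(−2.159) = 1.5%.

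**Second mechanism.** Here deaths are never missing, and loss depends on whether the mRS is 0–2 or 3–5. Results cover three assumed mRS distributions.

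- The same pattern in both arms: the OR changes by a factor of 0.997 to 1.003, which is practically nothing.
- BHC 2% throughout, DXM 1% (mRS 0–2) and 4% (mRS 3–5): 12–16% of the margin.
- BHC 5% throughout, DXM 3% and 10%: 30–37%.
- BHC 10% throughout, DXM 5% and 25%: 83–111%.

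Both mechanisms show that arm imbalance combined with dependence on outcome drives the bias. The overall missing rate alone does not.

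**The case against.** **The article does not support a size near the margin.** A reader might infer from the narrow limit that the exclusion shifts the result by about the whole margin. In the mixture model that takes no missing outcomes under BHC, 10% under DXM, and one third the odds in the missing. Under the second mechanism it takes a strong imbalance. The article gives no missing rate, arm difference or link to outcome, so these are possibilities and not predictions. This objection stands, and it is why the size is given as a range that includes no bias and the opposite direction.

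**The article limits the worst losses.** Death is mRS 6 in Table 1 and mortality is a separate outcome, so deaths should not be missing. There is an outpatient visit at 3 months besides the phone call. CRF data are monitored externally for completeness, and the DSMB reviews data completeness. These points lower the likely missing rate. They do not change the rule for whoever remains missing. The mixture model also moves the mRS 6 category, so it does not fully respect the first point; the second mechanism does.

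**Complete-case analysis can be valid.** It is unbiased if missingness depends only on arm and the adjusted baseline covariates, and the plan does adjust for prognostic variables. That is correct, but it ignores what the early and late mRS scores reveal about missing patients.

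**The exception is stated openly, and the SAP is not shown.** Analysing patients as randomised among those with an outcome is a known convention, so the wording is an inconsistency and not a concealed change. The SAP may hold sensitivity analyses for missing outcomes, and their absence from the article is not a finding. The exclusion rule itself is stated outright and can be judged as it stands.

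**Conclusion.** The point holds for the stated rule. Excluding patients without a 3-month mRS does not fit an analysis of all randomised patients, and it leaves unused the mRS planned at four other times while MICE serves baseline covariates only.

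The size is conditional. With missing patients at half the odds of a better outcome and a true OR of 0.90, the bias runs from none (equal missingness) through 13% and 32% of the margin (3% versus 5%, 5% versus 10%) to 65% (0% versus 10%). One-sided error rises from 2.5% to at most about 5.9% over that range. If the imbalance is reversed, the bias goes against DXM. The figures rest on assumed missing rates, the assumed k and an SE of 0.174, and they ignore any correction from baseline adjustment. Certainty is high that the rule exists and is improvable, and low about how much bias it would cause in this trial.

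**What to change.** Replace the exclusion rule in Data analysis. Add the 3-month mRS to the existing MICE model as a variable to be imputed, with treatment arm, baseline covariates and mRS at discharge, 2 weeks, 6 and 12 months as predictors. Known deaths by 3 months remain mRS 6, as Table 1 already has it. Analyse all randomised patients, and keep complete-case analysis as a sensitivity analysis. If the SAP does not already have one, add a delta-adjusted analysis that makes imputed DXM outcomes progressively worse and reports whether the conclusion against 0.9 still holds.

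The cost is a change of wording and a slightly larger imputation model; no new data are needed. The imputation assumes that outcomes are missing at random given these data, which is why the delta-adjusted analysis is useful. If the 3-month result is to be read out before 12-month follow-up ends, the plan must say which later scores enter the model. The change should be fixed before outcomes are seen by arm.

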**Fig. 2 Fig2:**
[figure not shown]
Flow diagram of main study procedures

In summary, study patients will be evaluated at presentation (baseline), during their hospital stay, at discharge and during the follow-up period at 2 weeks, 3 months, 6 months and 12 months.

At 2 weeks (after initiation of the study treatment) patients will be evaluated by neurological examination combined with a follow-up CT scan at the outpatient clinic or ward and at 3 months at the outpatient clinic. A mRS-certified research nurse, blinded for treatment allocation, will evaluate the primary outcome (mRS score) at 3 months by phone. At 3 and 12 months, patients will receive questionnaires on quality of life. Additionally, an evaluation of mRS score will take place by phone at 3, 6 and 12 months. Healthcare and productivity costs will be evaluated at 3 and 12 months. We expect to complete patient inclusion in 3 years. The estimated duration of the study (including follow-up) will be 4 years.

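### The QALY is tied to 12-month SF-36 and QOLIBRI summary scores, which are not utilities and say nothing about the months before

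*Protocol article*

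**What the plan says.** The Data analysis section plans an economic evaluation from a societal perspective. On the horizon it says: "The timeframe will be 12 months to take all relevant costs and effects into account". It describes the QALY as "quality-adjusted life year (QALY), based on the 12-month SF-36 and QOLIBRI summary scores" and adds that "the cost-utility analysis will use the QALY as effect measure". The same section makes the mRS the primary effect measure of the economic evaluation. The QALY stands beside mortality as a secondary one.

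On data collection, the Participant timeline says: "At 3 and 12 months, patients will receive questionnaires on quality of life". Secondary objectives and Secondary outcome measures give the same two times. The latter section also lists cost-effectiveness at 3 months as well as 12, and schedules the mRS at discharge, 2 weeks, 3, 6 and 12 months. One utility-type quantity is named there, "We will also determine a utility-weighted mRS (UW-mRS) at 3 months", but it is not linked to the QALY.

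On the expected course, the abstract states that "the benefit of DXM therapy appears much more deliberate than the immediate relief from BHC".

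**The concern.** A QALY is a preference weight, anchored at 0 for dead and 1 for full health, multiplied by the time lived at that weight. The stated rule departs from this in two ways.

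- **Scale.** SF-36 and QOLIBRI summary scores carry no such anchors. A patient who has died has no score, and the rule assigns none. It also cannot separate a death in month 1 from one in month 11.
- **Time.** A score at 12 months describes one moment. It cannot deliver the full-year account that the section gives as its reason for the 12-month horizon, and it cannot serve the 3-month cost-effectiveness evaluation listed among the secondary outcomes.

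At stake is the validity of the cost-utility comparison. If one treatment relieves symptoms at once and the other over weeks, much of any quality-of-life difference falls before 12 months, and a rule that reads only month 12 cannot see it.

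**Working it through.** The document gives no utility value, QALY figure or expected QALY difference, so there is no figure to reproduce. The check shows what weight each rule gives to each time point, and then what is lost under stated assumptions.

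**Inputs from the document.** Horizon 1 year; SF-36 at 3 and 12 months; mRS at 2 weeks, 3, 6 and 12 months.

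**Assumptions.** Equal utility in both arms at time 0; a gap d (BHC minus DXM) of 0.05 to 0.30 at 2 weeks; no gap at 12 months; straight lines between time points. Two weeks = 14/365 = 0.0384 year.

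**Step 1: weights.** Write Δ for the arm difference in utility (BHC minus DXM).

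- Literal rule, with the scores treated as if they were utilities: difference = 1 × Δ(12 months). Nothing before month 12 counts.
- Trapezoid on times 0, 0.25 and 1: QALY = 0.125(u0 + u3) + 0.375(u3 + u12). A common u0 cancels, so difference = 0.5 Δ(3) + 0.375 Δ(12).
- Trapezoid on times 0, 0.0384, 0.25, 0.5 and 1: the weight at 2 weeks is 0.25/2 = 0.125; at 3 months (0.5 − 0.0384)/2 = 0.2308; at 6 months 0.75/2 = 0.375; at 12 months 0.5/2 = 0.25.

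**Step 2: two assumed courses.**

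- (a) Gap closed by 3 months. True difference = 0.125 d. With times 0, 3 and 12 months: 0.5 × 0 = 0.
- (b) Gap d/2 at 3 months, closed by 6 months. True difference = 0.125 d + 0.2308 × d/2 = 0.2404 d. With times 0, 3 and 12 months: 0.5 × d/2 = 0.25 d.

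| Assumed gap d at 2 weeks | (a) true | (a) times 0, 3, 12 | (b) true | (b) times 0, 3, 12 | 12 months only, (a) and (b) |
|---|---|---|---|---|---|
| 0.05 | 0.006 | 0 | 0.012 | 0.013 | 0 |
| 0.10 | 0.013 | 0 | 0.024 | 0.025 | 0 |
| 0.20 | 0.025 | 0 | 0.048 | 0.050 | 0 |
| 0.30 | 0.038 | 0 | 0.072 | 0.075 | 0 |

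**Step 3: reading.** The 12-month rule returns 0 in every row. Adding the 3-month questionnaire helps only if some gap remains then. The close agreement in (b) comes from two errors that offset each other. Before month 3 the three-point curve gives 0.25 × (d/2)/2 = 0.0625 d, where the true area is 0.2404 d − 0.0625 d = 0.1779 d. After month 3 it gives 0.75 × (d/2)/2 = 0.1875 d, where the true area is 0.25 × (d/2)/2 = 0.0625 d. To see a gap that closes before 3 months, an earlier measurement is needed. The 2-week mRS is one.

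**The case against.** The best defence is that this is compressed wording. Value set, conversion and integration rule usually sit in an analysis plan; the article follows the Dutch guidelines for economic evaluation and points to a plan in Additional file 2, which is not at hand. SF-36 items can be turned into a utility index, and nothing in the text forbids it. The word 12-month may also mean the horizon named shortly before.

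Part of this stands. The absence of a value set or integration rule is not in itself a finding, and the full plan may contain both. But the sentence does more than omit: it names summary scores as the source, names QOLIBRI as one of them, and attaches 12-month to those scores. Read as the horizon, 12-month would ease the timing fault, but the scale fault would remain.

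A reader might also infer that quality of life is measured only once. It is not: both instruments are collected at 3 and 12 months, and the fault lies in which of these scores the QALY sentence uses.

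A reader might further infer a demonstrated bias in favour of DXM. The document does not support that. It supplies no utilities, and the Sample size section assumes an odds ratio of 1.15 for a better mRS with DXM, the primary mRS assessment being at 3 months. Course (b), with DXM still behind at 3 months, sits uneasily with that assumption. If DXM were ahead later in the year, the net effect of the rule could differ in size and direction.

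**Conclusion.** The point holds as a fault in a stated rule. Taken literally, the rule would not yield a valid QALY comparison, because its inputs are not utilities and it reads a single time point. It could miss an early difference of about 0.006 to 0.038 QALY if the gap closes by 3 months, and 0.012 to 0.072 if half of it persists to 3 months and closes by 6. Those figures rest wholly on the assumed gaps, shape and convergence by 12 months; they illustrate the loss and do not estimate it.

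The reach is limited. Cost-effectiveness at 12 months is one of the two primary endpoints, so a reader might infer that a primary endpoint fails. Its primary effect measure is the mRS, however, and the QALY is secondary within it. Nor does the point extend to the mRS-based ratio: the text does not say how the mRS is scored for it, and the planned cost-effectiveness plane and acceptability curves already display its uncertainty. The sentence should be corrected before analysis; it does not threaten the trial's main comparison.

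**What to change.** Replace the QALY sentence with a rule that fixes four things:

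1. QALYs are the area under the utility curve over 12 months.
2. Utilities come from a preference-based index derived from the SF-36 items, for example the SF-6D, at 3 and 12 months, with the value set named.
3. Utility is 0 from the date of death.
4. QOLIBRI is kept as a quality-of-life outcome and does not enter the QALY.

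Add one sensitivity analysis: an area under the curve from the utility-weighted mRS at 2 weeks, 3, 6 and 12 months, to cover the period before 3 months. The text states no baseline quality-of-life or mRS value (the schedule figure is not shown). If none is collected, state the starting utility as an assumption common to both arms; it then cancels from the arm difference.

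The cost is rewording and some programming, with no new visits. mRS-based weights and the SF-6D are different scales, so they should not be spliced into one primary curve. The primary QALY will therefore still be blind to a gap that opens and closes before 3 months, and only the sensitivity analysis addresses it.
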